### Objective 2: Identify and apply valid and reliable quantitative outcome measures to assess the impact of the enhanced resilience-based service delivery model for Aboriginal and Torres Strait Islander students using an interrupted time series design

An interrupted time series design will be applied to evaluate the effects of the resilience-based training and redefined model of student support in modifying mentees’ resilience, educational outcomes, and suicidal risk. The research design provides practicality and rigour by staggering implementation of the mentoring approach, enabling each group to act as a comparison group for itself and the other group [52]. This design is endorsed by the Cochrane Effective Practice and Organization of Care Group as an alternative to randomised control trials. The design is based on randomisation of the primary and secondary schools and groups of de-enrolled students supported by TSS staff into three clusters where students supported by TSS will receive the resilience-based model of student support starting 2016; 2017 and 2018 (Fig. 2).

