**Fig. 2 Fig2:**
[figure not shown]
Research deliverables

Selection criteria for the inclusion of schools will be collaboratively negotiated with TSS. The criteria will likely include: 1) having an enrolment of at least 10 TSS-supported students at the school and 2) being representative of the five TSS regions. We will also collect data for students from routinely available education indicators such as school attendance, retention. We will repeat the process with the second and third clusters of schools from 2017 to 2018.

We will assess the impact of the suicide prevention intervention on students’ resilience using: 1) routinely collected school outcomes data; and 2) screening survey data for the aggregated student cohort. Data routinely collected by Education Queensland (school attendance, retention and post-school destination) reflects suicide protective factors. Survey measures will be refined by the project steering group, but we anticipate a tailored instrument incorporating: resilience (individual capacities/ resources, relationships with primary caregivers and contextual factors that facilitate a sense of belonging), accompanied by the Kessler 5 psychological distress scale and suicidal risk factors, supplemented by questions assessing frequency of happy and angry feelings. Resilience will be measured using the Child and Youth Resilience Measure (CYRM) which has been validated internationally [53]. The suicide risk assessment questions are standard screening questions which were identified by a local Indigenous medical practitioner and CI as most relevant for Cape York students. The screening instrument will also include questions about services of which students are aware and access and transition strategies that they perceive to work. Using agreed measures, an online student screening survey will be integrated into TSS processes for student placements into boarding schools and administered using iPads to students in each cluster at the start of the 2016, 2017 and 2018 academic years.

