Taking account of an expected drop-out rate of senior students who complete school; and the high likelihood of tracing students due to the close linkages between TSS staff with students and their families, we expect a follow up rate of 80 % at mid-point (*n* = 412) and 80 % at post-intervention (*n* = 330). These sample size calculations are based on population measures and study design. The primary outcome measures will be resilience (measured using the CYRM), and school participation (measured through routine data and including a composite indicator comprising uptake of placements at boarding schools at start of grade 7; uptake of the first scheduled flights to boarding schools each term; and a reduction in the rate of suspension for students who re-engage for issues that relate to not staying enrolled). Based on previously conducted studies using ANOVA for analysis, we assumed a 10 % effect size [53]. This is very conservative. We assumed a standard deviation of (0.3). Sample size calculations for an alpha level of 5 %, with power 80 %, *n* = 68 students per group, which will sufficiently enable statistical testing of the hypothesised differences. Since we had planned to sample *n* = 172 mentored students per group, about three times the sample size required, we are confident that our sample will be adequate for additional group-specific stratified analyses. The identified results of the routinely collected and screening survey data will be fed back to TSS staff to tailor the development of mentees’ aspirational plans. Following the baseline screening survey, the same instrument will be implemented at the end of the academic year and upon completion of the following two academic years.

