A fixed cohort approach is planned [54] with the above-mentioned outcome measures for the 172 mentored students in group 1 compared pre- and post-intervention and to measures for the 172 students in groups 2 and 3. Separate statistical analyses will be undertaken for each outcome for each group using the statistical software program, STATA. The biennial proportion of students with each outcome of interest will be considered as a continuous measure for the analyses. Evaluation of the intervention effect in an interrupted time series design involves fitting a disjointed, segmented, linear regression model for the proportion of individuals with the outcome of interest over time, separately for each group. The models will include separate intercepts and slopes for both pre- and post-intervention (the two “segments”) and a term for site. For the intercepts, an intervention effect will be identified by a change or ‘jump’, in the primary outcome from pre- to post-intervention. For the slopes, an intervention effect will identified by a change in trend from pre- to post-intervention [55]. Examination of the magnitude of these coefficients will determine whether they are statistically significant.

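### The staggered comparison is announced but never enters the effect estimate: the only model is fitted within each group, so season, calendar shocks and maturation stay confounded with the intervention

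*Protocol article*

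**What the plan says.** All places are in the Protocol article, Objective 2.

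- **Design paragraph.** The staggered start is justified as "enabling each group to act as a comparison group for itself and the other group". Allocation is random: "The design is based on randomisation of the primary and secondary schools and groups of de-enrolled students supported by TSS staff into three clusters". Students in the three clusters "will receive the resilience-based model of student support starting 2016; 2017 and 2018".
- **Survey timing.** The student survey is "administered using iPads to students in each cluster at the start of the 2016, 2017 and 2018 academic years". In the sample-size paragraph, after baseline, "the same instrument will be implemented at the end of the academic year and upon completion of the following two academic years".
- **Analysis paragraph.** Outcomes for group 1 are to be "compared pre- and post-intervention and to measures for the 172 students in groups 2 and 3". The analyses are then described as separate for each outcome and each group, using a segmented "linear regression model for the proportion of individuals with the outcome of interest over time, separately for each group". The listed terms are an intercept and a slope before the intervention, an intercept and a slope after it, and site. The effect is defined as a jump in level or a change in trend from before to after, and significance is judged on those coefficients.

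**The concern.** The randomised stagger is the main strength of this design. At a given calendar time, clusters that have started can be compared with clusters that have not, and anything that moves all students alike cancels. The written model does not use this. Each group is fitted alone, with no term for calendar period or season and no coefficient that contrasts groups. The comparison of group 1 with groups 2 and 3 is announced in one clause, but it has no model and no place in the effect definition.

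Confounding is realistic here. The cohort is fixed, so students age through the study. The survey is built into placement into boarding schools, so group 1's baseline falls at the start of a school year, while the follow-ups named after it fall at year ends. The Background section itself describes transition stress and developmental change in these students. If such changes are read as a jump or a trend change, a positive (or null) finding on resilience, a primary outcome, could not be attributed to the programme.

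**Working it through.** The protocol gives no figure for drift over time, so there is no stated figure to reproduce. The drift sizes below are assumptions chosen for illustration. The yardstick is the 10 % effect in the sample-size paragraph, read as 0.10.

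**Inputs.** Starts in 2016, 2017 and 2018, each taken to fall just after that year's start-of-year survey (assumption: 0.05 year). Time is in years from the start of 2016, and a year-end survey is placed at 0.9 of the year. Fig. 2 is not shown, so two schedules common to all clusters were used:

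- A, four surveys: start 2016, then end 2016, 2017 and 2018 (t = 0, 0.9, 1.9, 2.9).
- B, six surveys: start and end of each year (t = 0, 0.9, 1, 1.9, 2, 2.9).

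**Step 1: can the model be fitted?** It needs four time coefficients per group (two intercepts, two slopes).

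| Group | Pre / post points, A | Pre / post points, B | Rank (of 4) |
|---|---|---|---|
| 1 | 1 / 3 | 1 / 5 | 3 |
| 2 | 2 / 2 | 3 / 3 | 4 |
| 3 | 3 / 1 | 5 / 1 | 3 |

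Group 1 has no estimable pre-slope and group 3 no estimable post-slope, on either schedule. Group 2 can be fitted, with 0 residual degrees of freedom under A and 2 under B.

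**Step 2: group 1 with zero true effect.** Estimate = mean of post surveys minus the single pre survey.

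- Year-end shift of 0.05: A gives 0.05; B gives (3/5) x 0.05 = 0.03.
- Linear trend of 0.05 per year: A gives 0.05 x (0.9 + 1.9 + 2.9)/3 = 0.095; B gives 0.05 x (0.9 + 1 + 1.9 + 2 + 2.9)/5 = 0.087.
- Calendar step of 0.05 from 2017: A gives (2/3) x 0.05 = 0.033; B gives (4/5) x 0.05 = 0.04.

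**Step 3: group 2, segmented fit, zero true effect.**

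| Assumed drift | A: jump / slope change | B: jump / slope change |
|---|---|---|
| Linear 0.05 per year | 0.000 / 0.000 | 0.000 / 0.000 |
| Year-end shift 0.05 | -0.008 / -0.056 | -0.019 / 0.000 |
| Calendar step 0.05 from 2017 | 0.050 / 0.000 | 0.021 / -0.030 |
| Curved, 0.02 x t squared | -0.028 / 0.078 | -0.031 / 0.078 |

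A linear trend is removed. The other three are not, and the signs differ.

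**Step 4: one pooled model.** With three group effects, survey-wave effects and an indicator switched on at each group's start, there are 3 + 3 + 1 = 7 columns under A and 3 + 5 + 1 = 9 under B. Both are full rank. Under all four drifts, taken as common to the groups, the estimated effect is 0.000.

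**Step 5: where the pooled contrast comes from.** Under A, no cluster has started at the first survey, one of three has at end 2016, two of three at end 2017, and all three at end 2018. Untreated comparators therefore exist only until cluster 3 starts.

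**The case against.** Several points on the other side have force.

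- **The comparison is stated.** A reader might infer that the plan drops every between-group comparison. It does not: group 1 is to be set against groups 2 and 3. What stands is narrower: that comparison has no model and does not enter the effect estimate. Further detail may sit in a fuller document, but the article fixes the model, its terms and the decision rule, and these are within-group.
- **Segmented regression handles trend.** It does where a pre-slope can be estimated, so it would be wrong to say that any change over time passes one-for-one into the jump. On the survey schedule this protects group 2 only, and only against a linear trend.
- **Routine data may reach further back.** School participation comes from routine records, including flight uptake each term, so a longer pre-series may exist. The fitting problem is shown here for the survey outcome only.
- **Adjustment to boarding is not uniform.** In 2015 the cohort had 114 Year 7 students, 261 already at boarding schools and 140 de-enrolled. Adjustment therefore does not coincide with the programme for every student, though ageing applies to all and season can.
- **The stagger still helps informally.** One can look at whether changes follow each group's start date or a single calendar date. That is not an estimate, and it does not deal with season or maturation.

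A reader might also turn an assumed drift into a false-positive rate by way of a paired test on individual students with the SD of 0.3. The documents do not support this: the planned regression is on group proportions, 0.3 is not stated to be an SD of change, and no drift is given.

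**Conclusion.** The point holds in this form: the protocol randomises the start dates to create comparators, then defines and tests the effect in models that never compare groups. For CYRM on common survey waves, group 1's estimate is a before-after difference confounded with season, ageing and adjustment, group 3's post-slope cannot be estimated, and group 2's fit is open to calendar shocks, season and non-linear maturation.

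The size of the bias is unknown and its direction can be either. In the illustrations, a 0.05 year-end shift gives group 1 a false effect of 0.03 to 0.05, and a 0.05 per year trend gives 0.087 to 0.095, against an assumed effect of 0.10. These rest on the assumed drifts and on the survey times as read from the text. If each cluster is instead surveyed only from its own start year, every group has a single pre-intervention point.

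**What to change.** Make the primary analysis one pooled stepped model on student-level data: survey-wave (calendar-period) fixed effects, group effects, an indicator for whether the student's cluster has started at that wave, and random effects for school and student. For school participation use the same structure, with periods that match the routine data. Report the per-group segmented models as descriptive.

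State that all three clusters are surveyed at every wave from the start of 2016. Untreated comparators then exist until cluster 3 starts in 2018, and the treatment contrast comes from the waves before that. The end-2018 wave has no untreated cluster.

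**Cost.** Standard errors will be wider than in a before-after model. If the survey sentence already means every cluster at every wave, only the analysis text changes. If it means each cluster from its own start year, clusters 2 and 3 need some earlier survey rounds. Without them no untreated cluster is observed alongside a started one at year end, and the pooled model has little to work with. The model removes drift that is common to the groups, not drift specific to one of them; for that it relies on the randomisation.

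### For CYRM, the per-group segmented regression needs a pre-intervention slope that cluster 1's single pre-intervention survey cannot supply, and depending on the survey schedule clusters 2 and 3 may fail too

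*Protocol article*

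**What the plan says.** All of this is in the protocol article under Objective 2.

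- **Staggered start.** Schools and groups of de-enrolled students are randomised into three clusters, which "will receive the resilience-based model of student support starting 2016; 2017 and 2018".
- **Survey timing.** The student survey is "administered using iPads to students in each cluster at the start of the 2016, 2017 and 2018 academic years". After baseline, "the same instrument will be implemented at the end of the academic year and upon completion of the following two academic years". The article also says: "We will repeat the process with the second and third clusters of schools from 2017 to 2018". No CYRM measurement before the start of 2016 is described.
- **Primary outcomes.** These are CYRM, taken from the survey, and school participation, taken from routine education records.
- **Model.** The closing paragraph of Objective 2 plans a "segmented, linear regression model for the proportion of individuals with the outcome of interest over time, separately for each group". It adds: "The models will include separate intercepts and slopes for both pre- and post-intervention", together with a site term. An intervention effect is to be read from a jump in level or from a change in trend.
- **Series.** The analysed quantity is "The biennial proportion of students with each outcome of interest".

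**The concern.** A slope over time needs at least two time points on its own side of the interruption. The plan asks for a slope on both sides, in each group separately, so no group can borrow a trend from another. The survey that supplies CYRM starts in the same year as cluster 1's intervention. The stated analysis and the stated schedule therefore do not fit together. This is a conflict between two things the article fixes, not a detail left to an analysis plan.

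At stake is one of the two stated criteria for an effect, the change in trend, on one of the two primary outcomes. The per-group model also contains no comparison between clusters. Yet the article justifies the staggered design by having each group serve as a comparison for itself and for the others, and it says group 1 will be compared with groups 2 and 3.

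**Working it through.** The plan gives no number of time points or residual degrees of freedom, so there is no stated figure to reproduce. Its sample size does not bear on the point, because more students do not add time points.

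**Inputs**

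- Four time parameters per group: intercept and slope before, intercept and slope after.
- Starts: cluster 1 in 2016, cluster 2 in 2017, cluster 3 in 2018.
- Survey dates as quoted above. The text allows several readings, so each is tried.
- Convention: a survey at the start of a cluster's own start year counts as pre-intervention. This is the reading most favourable to the plan; otherwise cluster 1 has none.

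**Formula**

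With *a* distinct pre-intervention and *b* distinct post-intervention survey times, the four-column design matrix has rank min(*a*, 2) + min(*b*, 2). The model is identified only if the rank is 4. Residual degrees of freedom (df) on group-level proportions are *a* + *b* − rank, before any site term.

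Example, cluster 1 with surveys at the start and end of each year 2016 to 2018: *a* = 1, *b* = 5, rank = 1 + 2 = 3. The pre-slope is not identified.

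**Results (pre/post surveys, rank, residual df where identified)**

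| Reading of the schedule | Cluster 1 | Cluster 2 | Cluster 3 |
|---|---|---|---|
| A. All clusters, start and end of 2016, 2017, 2018 | 1/5, rank 3 | 3/3, rank 4, 2 df | 5/1, rank 3 |
| B. All clusters, start of 2016, then ends of 2016, 2017, 2018 | 1/3, rank 3 | 2/2, rank 4, 0 df | 3/1, rank 3 |
| C. Own-start baseline only, then three year-ends | 1/3, rank 3 | 1/3, rank 3 | 1/3, rank 3 (1/2, rank 3 if cut at end 2019) |
| D. All clusters, starts of 2016, 2017, 2018 only | 1/2, rank 3 | 2/1, rank 3 | 3/0, rank 2 |
| E. All clusters at the three starts, plus three year-ends from each cluster's own start | 1/5, rank 3 | 2/4, rank 4, 2 df | 3/3, rank 4, 2 df (3/2, rank 4, 1 df if cut at end 2019) |

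The cut at end 2019 reflects the funding, which is for 5 years from December 2014. Under C and E, cluster 3's full follow-up would run to the end of 2020.

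- Cluster 1 fails in 5 of 5 readings.
- Cluster 3 fails in 4 of 5 (all but E). Under A, B and D this is because it has 0 or 1 post-intervention surveys; under C it lacks a pre-slope.
- Cluster 2 fails in 2 of 5 (C and D). Under B it has 0 residual df, so no significance test is possible on group-level proportions.

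**Does the site term or student-level data help?** No. With four sites per cluster (an assumption) and site indicators added, the model has 4 + 3 = 7 columns. Cluster 1's matrix has rank 6 of 7 in every reading, so it is still one short. Student-level rows add people at the same dates, not new dates.

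**The case against.** The strongest reply is that the defect is narrower than it first appears, and much of that reply stands.

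- **A reader might infer that the model cannot be fitted at all for CYRM.** The documents do not support that. Cluster 2 has two or three surveys on each side under A and B, and two and four under E, so both its slopes exist there, though weakly supported.
- **A reader might infer that at least two of the three groups must fail.** That depends on the reading. E uses all three timing sentences, and under it only cluster 1 fails. Fig. 2, which the article cites for the staggered starts, was not available and may settle the schedule.
- **A reader might infer that only a two-point before-after difference with no pre-trend remains.** Under A, cluster 2 has three pre-intervention points and cluster 3 has five, so both have a pre-trend. Only cluster 1 lacks one there, and it has five later points.
- **A reader might infer that the trial cannot answer its primary question.** The plan names two criteria, and the level jump is not necessarily lost. School participation comes from routine data, including flight uptake each term, and is not tied to the survey waves.
- **A reader might take biennial literally and conclude that there are about two points in all.** No stated survey schedule fits that. The article calls its forums biannual elsewhere, and twice-yearly would match A, so a slip of wording is likely. Under A, clusters 1 and 3 still fail.

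None of this rescues cluster 1.

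**Conclusion.** The point holds in this form: the per-group segmented model does not fit the CYRM survey schedule. In cluster 1 the pre-slope and the change in trend cannot be estimated under any of the five readings. In cluster 3 the post-slope cannot be estimated if surveys end in 2018. If each cluster has only its own-start baseline, no cluster has a pre-slope. Cluster 2 is estimable under some readings, with 0 to 2 residual df before the site term if surveys end in 2018.

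This rests on three things: no CYRM survey before the start of 2016, models fitted by group as written, and a survey at the start of the year counted as pre-intervention. The result for cluster 1 is firm. The results for clusters 2 and 3 depend on a schedule the text leaves open. The finding concerns the trend criterion for CYRM; it does not extend to the level criterion or to school participation as such.

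**What to change.** 1. **CYRM analysis.** Replace the three separate four-parameter models with one pooled analysis across the randomised clusters that estimates a single intervention effect from the staggered start. One suitable form is student-level repeated measures with calendar-wave effects and random effects for school and student; other pooled forms are possible. This also supplies the between-group comparison the article promises. Under A, four of the six waves (end 2016, start 2017, end 2017, start 2018) contain both clusters that have started and clusters that have not.
2. **Survey waves.** State in one sentence that all three clusters are surveyed at every wave from the start of 2016. The pooled model needs this. Under C, every start-of-year survey is pre-intervention and every year-end survey is post-intervention, so the effect could not be separated from the wave effects.
3. **Frequency.** Replace biennial with the actual wave frequency.
4. **Segmented regression.** Keep it only for routine school data, where enough time points before 2016 are available.

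The cost is analysis wording, one sentence on the waves, and extraction of earlier routine records. The downside is that there would be no per-group CYRM trend-change estimate, which cluster 1's data cannot give in any case.

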### The participants

We will work with TSS staff as mentors (24) and students as mentees (515) (*n* = 539). The mentors include all management, Transition Support Officers, Community Support Officers and Youth Mentors across the three streams of TSS: 1) transition from the primary to secondary phase of schooling; 2) engagement with secondary schooling and transition to work, training or further education at completion of Year 12; and 3) re-engagement with learning, training or employment pathways when enrolment at boarding schools is not an option. Mentees include the entire cohort of students assisted by the TSS: in 2015, 114 Year 7 students and families; 261 secondary school-aged students at boarding schools; and 140 students who have become de-enrolled from boarding schools and who have returned to their communities.

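### The resilience analysis models wave-level proportions in a cohort expected to fall from 515 to 330, and cannot tell change within students from change in who responds

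*Protocol article*

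**What the plan says.** All of this is in the protocol article, under The participants and Objective 2.

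- **Cohort.** The mentees number 515: 114 in Year 7, 261 at boarding schools, and "140 students who have become de-enrolled from boarding schools and who have returned to their communities".
- **Expected follow-up.** The paragraph on sample size begins "Taking account of an expected drop-out rate of senior students who complete school". It also cites a high likelihood of tracing students, then states "we expect a follow up rate of 80 % at mid-point (*n* = 412") and "80 % at post-intervention (*n* = 330").
- **Cohort type.** The analysis paragraph opens with "A fixed cohort approach is planned". It compares the 172 students of group 1 before and after the intervention, and with groups 2 and 3.
- **Analysed quantity and model.** The outcome in the model is the proportion of students with the outcome over time. A segmented linear regression is fitted to it separately in each group, with pre and post intercepts and slopes and a site term.
- **Decision rule.** For the intercepts, "an intervention effect will be identified by a change or" jump between the two segments; for the slopes, by a change in trend.
- **Timing.** The clusters start in 2016, 2017 and 2018. The survey is given at the start of the first year, at its end, and at the end of the next two academic years.
- **Outcomes.** The primary outcomes are resilience on the Child and Youth Resilience Measure (CYRM), which comes from the survey, and school participation, which comes from routine data.

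**The concern.** A wave's proportion can be calculated only for students who answered at that wave. When the later waves contain fewer students than the earlier ones, the proportion can move for two reasons: students changed, or the set of students changed. The stated model has terms for time segment and site, and none for student, age or year level, so it cannot separate the two.

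The article's own account makes non-random loss plausible. The loss it anticipates is of senior students, so it is related to age. The programme also aims to change school participation, so it may alter who remains reachable for the survey.

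The fixed-cohort statement suggests that the same students are followed, but the article does not say which students enter each wave's proportion. At stake is the primary resilience outcome: selective loss could be reported as benefit, or could hide it.

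**Working it through.** **1. The plan's own figures.** 515 × 0.80 = 412. 412 × 0.80 = 329.6, rounded to 330. 330/515 = 64.1% retained, so about 36% are lost by the last wave. Per group, 172 × 0.64 ≈ 110. The stated figures reproduce.

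**2. Simplest case: no student's outcome changes.** Let L be the share lost, and p_R and p_L the proportions with the outcome among students retained and lost. The full-cohort proportion is (1 − L)·p_R + L·p_L, so the shift when only the retained are counted is

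shift = L × (p_R − p_L).

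The gap p_R − p_L is not in the documents, so a range is shown.

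| Assumed gap (points) | Mid-point, L = 0.20 | Post-intervention, L = 0.36 |
|---|---|---|
| 0 | 0 | 0 |
| 10 | 2.0 | 3.6 |
| 20 | 4.0 | 7.2 |
| 30 | 6.0 | 10.8 |

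A comparison of the same students at both waves gives exactly 0 in this case.

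**3. Scores that fluctuate, with no average change.** This was a simulation with N = 400,000. Baseline score x and later score y are standard normal with correlation 0.5 or 0.7. The outcome is a score above the baseline median. The log-odds of staying are a + ln(OR) × score, with a set so that 64.1% stay. OR is 1.0, 1.5 or 2.0 per SD, and loss depends either on x or on y. Correlations, odds ratios and the cut-point are assumptions.

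| Loss depends on | All responders, pre to post | Students seen both times |
|---|---|---|
| nothing (OR 1.0) | 0 | 0 |
| baseline score (OR 1.5–2.0) | about +3 to +6 points | about −2 to −5 points |
| current score (OR 1.5–2.0) | about +6 to +9 points | about +2 to +5 points |

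If more resilient students are the ones who leave, every sign reverses. As a check against step 2, the simulated gaps between retained and lost were 8 to 26 points. 0.36 × 8 = 2.9 and 0.36 × 26 = 9.4, which agrees with 3 to 9.

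**4. What conditioning on the baseline score achieves.** The bias is about 0 when loss depends on baseline. When loss depends on the current, unobserved score, 0.07 to 0.18 SD remains.

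**5. Timing.** Steps 2 and 3 compare two waves and place all the loss after the pre wave. That fits group 1 best: if the survey at the start of 2016 is its only pre-intervention wave, all its loss comes later. In groups 2 and 3 some loss precedes the intervention and may load on the slope.

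**The case against.** The strongest reply is that a fixed cohort most naturally means the same students followed over time, and that a same-student comparison gives exactly 0 when no student changes. That is correct for unchanging outcomes. It does not settle the matter, because the article does not say that wave proportions are restricted to students seen throughout. Once scores fluctuate, the restricted comparison can also be biased, in either direction depending on what drives loss.

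A reader might infer that a false jump is bound to appear, and in every group. The documents do not support that. They give no difference in resilience between students retained and lost, they expect good tracing, and random loss gives 0. De-enrolment is not loss either, since 140 de-enrolled students are in the cohort. Comparison between groups may offset attrition that they share, although the models are fitted separately and a programme that changes engagement need not leave attrition equal.

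A reader might also infer that the artefact is a large part of the planned 10% effect. The scales do not match. If the 10% is 0.1 on a scale with the stated SD of 0.3, it is 0.33 SD, or about 13 points on a median cut. If it means percentage points, it is 10. The article does not say which.

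Finally, detailed missing-data handling may sit in an analysis plan that is not shown, and its absence here is no finding. The point rests on what the article does fix: the analysed quantity, the model terms and the rule for declaring an effect.

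**Conclusion.** The point holds in a conditional form. The article plans for 36% cumulative loss and fixes an aggregate-proportion model that cannot distinguish change within students from change in who responds. It leaves open which students form each wave's proportion.

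Under the assumptions in step 3, the responder artefact on the CYRM outcome is 0 points with random loss and about 3 to 9 points with selective loss. Restricting to students seen throughout leaves about −2 to −5 points if loss depends on baseline and +2 to +5 if it depends on current score. These sizes rest on assumed odds ratios and correlations, an assumed cut at the baseline median, and a two-wave layout rather than the full segmented model. The direction is not known in advance. School participation comes from routine data and is not affected in the same way.

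**What to change.** For the CYRM outcome, replace the regression on wave proportions with a student-level repeated-measures model that uses every observed wave of every enrolled student. Keep the pre/post and site terms. Include the baseline score, stream or year level, and routine enrolment and attendance as predictors or auxiliary variables where records can be linked. State explicitly that all enrolled students contribute, so that the fixed-cohort statement and the model agree.

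This removes the bias when loss depends on those observed variables. It does not when loss depends on the current unobserved score, so add one delta-adjusted sensitivity analysis that shifts the assumed CYRM of non-responders. Because the sign is unknown, the shift should cover both directions.

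For school participation, only confirm that it is analysed for all consented students whether or not they answer the survey.

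The cost is somewhat more modelling and the need to link survey and routine records by student. The survey waves and routine indicators are already planned. The article does not say whether routine records continue for students who have finished school; if they do not, the model must rely on baseline score and stream or year level for them.
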